#### The design

This is a 3-arm randomized controlled trial (RCT) with the following: a control group, with no program; an intervention group, with the online narrative-based program; and an enhanced-intervention group, with the online narrative-based program with gamification strategies embedded in the program. Both intervention groups (i.e., the intervention group and the enhanced-intervention group) will have the same narrative-based intervention described in Table 1. The only difference between the two intervention groups is that, in the enhanced online intervention group, gamification strategies will be added to the dynamics of the program. No other intervention components, timings, and materials will differ between these two trial arms. Despite the potential advantages of conducting online interventions, literature on digital interventions to promote behavior change has highlighted that this mode of delivery is associated with high rates of dropout [39]. Thus, one concern among researchers in this field is to devise strategies that mitigate the high rates of dropout and instill engagement in the online intervention [39, 40]. Accordingly, we are implementing the additional gamification strategies in the third group to assess the efficacy of these strategies in promoting engagement with the program and activities.

Gamification consists in the use of game design elements in a non-game context [41]. Non-game contexts can be education [42], health [43], and business [44]. Examples of game design elements are the narrative context, feedback, reputation, ranks, levels, competition, and relational support [41]. Considering the engaging nature of games, it is expected that adding some of their design and motivational features to the non-game contexts [41, 45, 46] will contribute to the (i) creation of engaging and fun contexts or environments, (ii) enhancement of the degree and depth of participants’ engagement, (iii) promotion of learning opportunities, and (iv) motivation of individuals to engage in the task at hand. Table 2 illustrates how gamification was infused in the online program for the enhanced online intervention group.

**Table 2 Tab2:** Gamification elements used in the enhancement-treatment group

Elements*	Objective/rationale**	How it was implemented

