### Goals and expected outcomes

The main purpose of this study is to evaluate the efficacy of an online intervention, narrative-based with or without gamification strategies, designed to promote healthy eating by fostering the use of SR strategies among elementary school-aged children. Thus, the major goals are to promote children’s use of SR strategies for healthy eating, to strengthen their sense of self-efficacy regarding healthy eating, and to increase the consumption of healthy foods. Other goals of the study include the following: increase knowledge about healthy eating and consequences of unhealthy nutrition or lifestyle; contribute to healthier food preferences; and contribute to more positive attitudes and perceptions about healthy eating. Thus, we want to assess the feasibility of conducting an online intervention with this population and examine the advantages of embedding the program with gamification strategies, by comparing it to the program without these strategies.

Overall, it is expected that children taking part of the intervention will, at the end of the intervention, increase their use of SR strategies for healthy eating, enhance their sense of self-efficacy for healthy eating, and increase their consumption of healthy foods. Additionally, it is expected that their knowledge on the topic will increase, that their food preferences become healthier, and that they will display perceptions and attitudes about the topic that are more positive. Lastly, it is expected that participants enrolled in the enhanced-online-intervention group will be more engaged in the intervention than the online-intervention group.

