### Primary and secondary outcome measures

The primary outcomes will be the analysis of differences in SR, self-efficacy, knowledge towards healthy eating, and, additionally, the amount of healthy and unhealthy food consumption at baseline (*T*_0_), final (*T*_1_), and follow-up (*T*_3_, *T*_4_) assessments. Secondary outcome measures will include the anthropometric (i.e., body mass index [BMI] *Z*-scores), sociodemographic variables (−T_1_), other healthy behaviors (e.g., screen time and physical activity), psychological (e.g., attitudes and perceptions about healthy eating), and engagement (e.g., weekly journal) measures. Differences within the group (i.e., at baseline, final, and follow-ups assessments), as well as between groups (i.e., control, online-intervention, and enhanced-online-intervention), will be tested over time. The repeated measures assessment allows testing relevant factors affecting SR and self-efficacy on healthy eating and food consumption. Additionally, weekly engagement indicators collected with the journals and with the actual interactions with the platform will be tested as predictors of primary outcome measures in final and follow-up assessments. Lastly, moderators and mediators that can affect the outcomes of the intervention but that are not predictor variables include sex, socioeconomic level, and academic achievement.

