### Statistical analysis plan

The effectiveness of the HEP-S intervention will be assessed using linear mixed-effect models. Specifically, we will assess the impact of interventions groups vs. control group on changes over time regarding the primary outcomes (e.g., healthy eating behavior, SR, self-efficacy towards healthy eating). For that, we will first examine within-intervention group differences (i.e., over time) followed by between-intervention group assessments at each time point. Differences between groups will be supported if the beta-weight parameter for the interaction between group and time are statistically significant.

Moreover, statistics descriptive analyses will be computed to describe all participants’ characteristics by using chi-square tests and independent tests to compare groups on the distributions according to sex, age group, BMI *Z*-score classification, and others. In addition, secondary outcomes will be analyzed by using similar models, comparing the three research groups. Also, these secondary repeated measures (e.g., satisfaction with the program) will be examined by conducting an analysis of covariance to explore interference with main outcomes. Finally, no interim analyses of the primary and secondary outcomes are planned to be included in this trial.

All analyses will be completed by using SPSS software (version 26), and *p* values below .05 will be considered statistically significant. The normality, homoscedasticity, and linearity of the residuals of each model will be examined to ensure that the assumptions of the models are met.

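### The only stated criterion for a group difference, a significant group-by-time interaction, cannot register a steady engagement advantage for the gamified arm

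*Protocol article*

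**What the plan says.** All references are to the protocol article.

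- **Criterion.** Statistical analysis plan: "Differences between groups will be supported if the beta-weight parameter for the interaction between group and time are statistically significant". The sentence before it plans within-group comparisons over time, "followed by between-intervention group assessments at each time point".
- **Reach.** The next paragraph of that section says "secondary outcomes will be analyzed by using similar models, comparing the three research groups". Primary and secondary outcome measures lists "engagement (e.g., weekly journal) measures" among the secondary outcomes and says that differences within and between groups will be tested over time.
- **Hypothesis.** Goals and expected outcomes: "it is expected that participants enrolled in the enhanced-online-intervention group will be more engaged in the intervention than the online-intervention group". The design section says the gamification arm was added "to assess the efficacy of these strategies in promoting engagement with the program and activities".
- **Measurement.** The Engagement section takes the data from children's activity on the online platform. The Journal section adds weekly questions on engagement during that week. Table 3 gives the journal to the intervention groups weekly only; its baseline and final entries are for the control group.
- **Tested parameter.** Definition of the hierarchical model sets the null hypothesis as γ101 = 0, the treatment-by-linear-trend interaction. The model also contains a group term, γ001, which is not named as a test.

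**The concern.** A group-by-time interaction measures a treatment effect when the arms share a pre-treatment starting value. That is true of self-regulation, self-efficacy and knowledge, which Table 3 measures at T0 in every arm. It is not true of engagement. Platform activity cannot precede the program, and the program arms complete no journal at T0. According to Table 2 the gamification rules are explained in the first session and rankings appear every week, so the first engagement values may already carry the effect.

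For such an outcome the interaction shows only whether the gap between the arms widens or narrows. It does not show whether one arm was more engaged, which is what the protocol expects. At stake is the conclusion of the enhanced-versus-standard comparison, the stated reason for the third arm.

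**Working it through.** **The plan's own figure.** The article reports a minimum detectable effect of 0.25 for the interaction. Inputs: N1 = 5, N2 = 15, N3 = 40, ρ1 = 0.5, slope-variance ratio τ = 0.1, two-sided α = 0.05; Var(T) = 2 for occasions 0 to 4.

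- z = (0.25/4) × √[5×15×40×2 / (2×(0.5 + 5×2×0.1))] = 0.0625 × √2000 = 2.795
- Power = Φ(2.795 − 1.96) = 0.798; minimum detectable effect 0.251

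This agrees with the article when the two denominator terms are added. As printed, equation 6 multiplies them and gives 0.998. That is a separate matter, and nothing below depends on it. What it shows is that the planned power is for γ101.

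**Constant gap under the interaction criterion.** Let the gap be d in each of 20 weeks. The slope contrast is d × Σ(week − 10.5) = 0, so γ101 = 0 for every d. With categorical time every group-by-week term is also zero. The test then rejects at its error rate. A simulation (4,000 runs, 40 classes of 15 per arm, variances 0.5, 0.3 and 0.2) gave:

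| d (SD) | Interaction significant | Mean difference significant |
|---|---|---|
| 0.25 | 0.050 | 0.652 |
| 0.5 | 0.050 | 0.997 |
| 1.0 | 0.051 | 1.000 |

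Adding a class slope variance of 0.1 on a centred time axis of length 1 left this unchanged: interaction 0.048 to 0.052, mean difference 0.642, 0.997 and 1.000. Centring keeps the slope out of the mean, so that run does not test the case below.

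**Power of the 20-week mean, by formula.** The SD is that of the total variance, 0.5 + 0.3 + 0.2 = 1.

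*No slope variance:*
- Var = (2/40) × (0.2 + 0.3/15 + 0.5/300) = 0.0111; SE = 0.105
- d = 0.25: Φ(2.375 − 1.96) = 0.66
- d = 0.5: Φ(4.749 − 1.96) = 0.997

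*The plan's class slope variance of 0.1, rescaled from occasions 0–4 to weeks 0–19:*
- Per week squared: 0.1 × (4/19)² = 0.00443
- With time starting at 0 the mean week is 9.5, so the class slope adds 0.00443 × 9.5² = 0.40
- Var = (2/40) × (0.2 + 0.40 + 0.02 + 0.0017) = 0.0311; SE = 0.176
- d = 0.25: Φ(1.418 − 1.96) = 0.29
- d = 0.5: Φ(2.836 − 1.96) = 0.81

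**Fading gap, 0.5 SD to 0 over weeks 0–19.** The slope is −0.5/19 = −0.0263 and the sum of squares of week is 665.
- No slope variance: SE = √[0.05 × 0.5/(15×665)] = 0.00158; z = −16.6
- Slope variance 0.00443: SE = √[0.05 × (0.00443 + 0.00005)] = 0.0150; z = −1.8

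**The case against.** **The criterion says if, not only if, and comparisons at each time point are planned.** Both are true. A reader might infer that the plan forbids any other evidence of a difference; it does not say so. Yet no other basis for support is stated, and the time-point comparisons come with no rule for combining up to 20 weekly results into one answer about engagement.

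**The criterion belongs to the primary outcomes.** Its paragraph opens with them, and the reference to similar models may carry over only the model family, which includes a group term. So the rule reaches engagement by extension, and the point must be put conditionally. The extension is still the natural reading, because the outcomes section says group differences will be tested over time and no other criterion is given.

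**The three-group sentence cannot be meant for engagement, since controls have no platform activity.** On that view the engagement analysis is merely left out of a condensed article. But engagement is listed among the outcomes that the sentence covers. The mismatch is a further reason to name the two arms.

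**Weekly modelling is an assumption.** The article's engagement examples are counts, and a program total has no time factor. The interaction criterion then cannot be applied at all, and no criterion remains.

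**Gamification may work by slowing a decline.** The article motivates it partly by dropout, and points accumulate. An interaction would detect such a pattern. That is a good reason to keep the term, but the written expectation is "participants enrolled in the enhanced-online-intervention group will be more engaged in the intervention than the online-intervention group", which a steady gap would satisfy.

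**Conclusion.** The point holds in conditional form. If the stated criterion is applied to engagement, a constant advantage for the gamified arm, however large, is supported only about 5% of the time. This follows from the algebra and does not depend on the variances.

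The power of the better comparison does depend on them. It is about 66% at 0.25 SD and 99.7% at 0.5 SD with no slope variance, against about 29% and 81% with the plan's 0.1 rescaled to weeks and time starting at 0. These figures assume 40 classes of 15 per arm, 20 weekly values and the article's hypothetical variances. The article gives no engagement effect or variance, and no school-level variance is included.

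A reader might go further and infer that an advantage that fades would come out as strong evidence against gamification. The documents do not support that. The large negative z of −16.6 needs zero slope variance; with the plan's own value rescaled it is about −1.8, short of significance.

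Engagement is a secondary outcome and the wording leaves room for a sensible analysis, so this should be fixed but is not critical.

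**What to change.** Add to the Statistical analysis plan section that engagement is exempt from the interaction criterion. It is compared between the enhanced and standard online arms only, on mean engagement over the 20 program weeks, or on the program total for counts. Class and, for the weekly values, child random effects are retained. Keep group-by-week as a secondary description of whether the gap grows or fades.

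Define the contrast explicitly as the 20-week mean. In the article's model the group term is the gap at T = 0 unless time is centred, so naming the group main effect alone would not be enough.

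The interaction criterion can stay for outcomes with a T0 value in all arms. The change costs a sentence or two and needs no new data.

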**Methods:**

A three-armed randomized controlled trial will be conducted in several schools in Portugal. It will include a standard control group, with no intervention; an online intervention group, with the program for 20 weeks; and an enhanced online intervention group, with the program for 20 weeks embedded with gamification strategies throughout the program. Per research group, 40 groups of about 15 children each will be recruited and measured at five different time points. The three research groups will complete the same assessment protocol at the same timings (baseline, post-intervention, and 3, 6, and 9 months’ follow-ups). The assessment protocol will include anthropometric and psychological measures. The primary outcome measures will be the development of self-regulation skills for healthy eating over time, the development of self-efficacy attitudes, knowledge about healthy eating over time, and others. The secondary outcome measures will include the effect of gamification strategies, engagement, and satisfaction with the program, among others. The program will comprise the following: (i) a weekly group synchronous videoconference session with a trained educational psychologist serving as a mediator and (ii) a weekly parental involvement activity. Narratives, or story-tools, embedded with self-regulation strategies are at the core of the intervention.

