### Proposed sample size

Considering this longitudinal design, in the calculation of the sample, we considered a 0.25 effect size, an alpha level of 0.05, a desired statistical power of 0.8, five measures, and three research groups (i.e., control, online intervention, enhanced online intervention). To run a three-level cluster-randomized trial, previous analysis suggested 40 groups per group condition with 15 participants in each, measured at five different time points (see section “Definition of the hierarchical model”).

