### Assessment

Table 3 illustrates the timeline for the different assessment measures of the children participating in this project.

**Table 3 Tab3:** Timeline for the different assessment measures of the project

Measures	Registration (−T1)	Baseline assessment (T0)	Final assessment (T1)	3-month follow-up assessment (T3)	6-month follow-up assessment (T4)	Weekly assessment
Eligibility screen	X	–	–	–	–	–
Informed consent	X	–	–	–	–	–
Anthropometric	X	–	X	X	X	–
Sociodemographic	X	–	X	X	X	–
Self-Regulation^1^	–	X	X	X	X	–
Self-efficacy^2^	–	X	X	X	X	–
Declarative knowledge^3^	–	X	X	X	X	–
Attitudes and perceptions^4^	–	X	X	X	X	–
Healthy eating and physical activity behaviors^5^	–	X	X	X	X	–
Satisfaction	–	–	Intervention groups	–	–	–
Journal	–	Control group	Control group	–	–	Intervention groups

*X* available to all groups

^1^Self-Regulation Processes towards Healthy Eating Questionnaire

^2^ Self-Efficacy to Regulate Eating Habits for Children Questionnaire & Healthy Eating and Physical Activity Self-Efficacy questionnaire for children

^3^ Knowledge of Healthy Eating Questionnaire

^4^Students’ Attitudes and Perceptions on Healthy Eating Questionnaire

^5^ Healthy Eating and Physical Activity Behavior Recall Questionnaire for Children

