As Heo et al. [54] and others (e.g., [55]) have indicated, the most important goal of a longitudinal intervention is to test whether there are differences between intervention groups with respect to their average growth rates. Applying the approach of these authors, the power to detect a specified treatment difference between average rates of change for the groups is defined as the probability of rejecting the null hypothesis of no treatment-by-linear-trend interaction *H*_0_: γ_101_ = 0, given that it is fact false (γ_101_ ≠ 0). This hypothesis can be tested with
5$$ {F}_o=\frac{{\hat{\gamma}}_{101}^2}{Var\left({\gamma}_{101}\right)}=\frac{\Delta^2\left[{N}_1{N}_2{N}_3 Var(T)\right]}{2\left(1-{\rho}_1\right){\sigma}^2{N}_1 Var(T){\sigma}_{u1}^2}, $$

where Δ is the effect standardized effect size at the last time point, *N*_1_ is the number of level 1 units (repeated measures) per student, *N*_2_ the number of level 2 units (students) per classroom, *N*_3_ the number of level 3 units (classroom) per treatment condition, *Var*(*T*) is the population variance of the time variable *T*, $$ {\upsigma}_{u1}^2 $$ is the three-level random slope variance, σ^2^ is the sum of the other variances, and *ρ*_1_ is the correlation between outcomes measures at different time points on the same student nested within classroom.

The power of the test statistic *F*_0_, denotes 1 − *β*, can be written as follows:
6$$ 1=\beta =\phi \left\{{\left\{\frac{\Delta }{\left({N}_1-1\right)}\left[\frac{\left[{N}_1{N}_2{N}_3 Var(T)\right]}{2\left(1-{\rho}_1\right){\sigma}^2{N}_1 Var(T){\tau}_s}\right]\right.}^{\frac{1}{2}}-{Z}_{1-\left(\alpha /2\right)}\right\}, $$

where τ_*s*_ is the ratio of the three-level random slope variance to the sum of the other variances, ϕ is the cumulative distribution function of a standard normal distribution, and *Z*_1 − (α/2)_ is the 100 (1 − *α*/2) percentile of the standard normal distribution for a bilateral test.

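### Several unranked primary outcomes are each tested at p < .05, with no rule across outcomes or arm contrasts, and the status of knowledge differs between sections

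*Protocol article*

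**What the plan says.** **Primary outcomes.** The section on primary and secondary outcome measures lists "differences in SR, self-efficacy, knowledge towards healthy eating, and, additionally, the amount of healthy and unhealthy food consumption" as primary, at baseline, final and follow-up assessments, with no order of importance. The footnote to Table 3 gives self-efficacy two instruments: "Self-Efficacy to Regulate Eating Habits for Children Questionnaire & Healthy Eating and Physical Activity Self-Efficacy questionnaire for children". That makes four domains and up to six scores, if both self-efficacy scales count and healthy and unhealthy food are counted separately.

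**The same list elsewhere.** The goals section makes SR, self-efficacy and consumption the major goals and then says "Other goals of the study include the following: increase knowledge about healthy eating". The abstract names SR, self-efficacy and "knowledge about healthy eating over time, and others". The statistical analysis plan section gives examples only, and knowledge is not among them.

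**Decision rule.** The same section bases a claim of a group difference on a significant group-by-time interaction. It also plans within-group comparisons over time and between-group comparisons at each time point. For all analyses, p "values below .05 will be considered statistically significant".

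**Sample size.** The calculation states: "we considered a 0.25 effect size, an alpha level of 0.05, a desired statistical power of 0.8, five measures, and three research groups". The power formula is written for one hypothesis, γ101 = 0, using the "percentile of the standard normal distribution for a bilateral test". The model has one group variable G_j and one interaction coefficient, although there are three arms.

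**The concern.** With several primary outcomes, a plan needs a rule for success: all must succeed, one is decisive, or the error rate is shared. This plan has none. Nor does it say whether the two programme arms are pooled against control or compared with it separately. A reader of the results could take one significant interaction out of several as proof of efficacy, and the nominal 5% would not describe the risk of that claim being false.

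The unsettled status of knowledge adds to this. A result on knowledge alone would be a primary success under the outcomes section and a subsidiary finding under the goals section, and the choice could be made after the data are seen.

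**Working it through.** **1. The plan's own figure.** Inputs from the section defining the hierarchical model: residual variance 0.5, student intercept 0.3, student slope 0, classroom intercept 0.2, classroom slope 0.1, ρ1 = 0.5, N1 = 5, N2 = 15, N3 = 40. With T = 0 to 4, Var(T) = 2, and σ² = 0.5 + 0.3 + 0.2 = 1. Reading the denominator of the power formula as a sum:

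- Var(γ101) = 2 × [(1 − 0.5) × 1 + 5 × 2 × 0.1] / (5 × 15 × 40 × 2) = 3 / 6000 = 0.0005, so SE = 0.02236.
- Minimum detectable effect = (5 − 1) × (1.960 + 0.842) × 0.02236 = 0.251.
- Power at 0.25: (0.25 / 4) / 0.02236 = 2.795, and Φ(2.795 − 1.960) = 79.8%.

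The stated 0.25 at 80% is reproduced. It has one contrast, one outcome and α = .05 in it, and no term for a third arm or further outcomes. (The product form as printed gives 0.145. That, and whether the formula suits the model, are separate matters; the formula is used here only to price the change.)

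**2. Chance of at least one false claim.** Assumptions: no true effect on any outcome in any arm; one two-sided .05 interaction test per outcome and contrast; any one significant result read as efficacy; equal arms (1:1:1), so contrasts share arms; a common correlation r between outcomes. The documents give no r, so a range is shown. Simulation with 400,000 draws, four outcomes:

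| Contrasts per outcome | r = 0 | r = 0.3 | r = 0.5 | r = 0.7 |
|---|---|---|---|---|
| One (arms pooled against control) | 19% | 17% | 16% | 13% |
| Two (each programme arm against control) | 32% | 30% | 27% | 23% |
| Three (all pairs) | 41% | 38% | 34% | 29% |

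The one-contrast entry at r = 0 agrees with 1 − 0.95⁴ = 18.5%. If all six scores counted, the ranges would be about 16-27%, 28-44% and 35-54%.

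**3. Price of control, on the authors' SE.**

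- One named contrast at .025: Φ(2.795 − 2.241) = 71%.
- Holm over two contrasts sharing the control arm, both true effects 0.25 (simulated): about 76% power for each contrast; the smaller p-value passes .025 about 85% of the time.
- Bonferroni over four outcomes and two contrasts (α = .05 / 8 = .00625): about 53%.

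**The case against.** **The plan does have a decision rule.** It ties group differences to the group-by-time interaction. This stands. A reader might infer that every within-arm or per-visit test at .05 is a route to success; the documents do not support that, and the figures above leave those tests out.

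**The percentages are conditional.** This also stands. They need a global null, an any-one-wins reading that the document neither adopts nor excludes, and assumed correlations. The wording of intervention groups against control, with a single G_j, can mean one pooled contrast, which gives the lowest range. The goals section plans to compare the enhanced with the plain programme, but its stated expectation there is better engagement, a secondary outcome, so the three-contrast row is the least secure.

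**The lists are condensed rather than contradictory.** Partly right. The abstract's open ending and the examples in the analysis section may only shorten the full list. The real conflict is knowledge: an other goal in one section, primary in another.

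**Multiplicity belongs in a separate analysis plan.** A silent article could rely on that. This one has its own analysis section, which sets .05 for all analyses, and following it as written inflates the error rate.

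**Conclusion.** The concern holds in this form: four unranked primary domains (up to six scores), a flat .05 for each group-by-time interaction, no rule across outcomes or the two intervention-versus-control contrasts, and an inconsistent status for knowledge. If one significant primary interaction is taken as efficacy, the global-null error for four outcomes is 13-19%, 23-32% or 29-41%, depending on the contrasts tested. Even the lowest range is about three to four times the nominal 5%. No single percentage can be given as the trial's error rate, because the contrasts, the success rule and the correlations are not fixed in the document.

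A reader might also infer that the 80% power means nothing for this trial. That goes too far. It is a figure of the right kind for one group-by-time contrast on one outcome at .05; it does not describe power for a set of outcomes and contrasts with a controlled error rate.

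**What to change.** 1. Use one primary list in the abstract, the goals, the outcomes section and the analysis section, and settle whether knowledge is on it.
2. Name one primary score, for example the SR questionnaire, and keep the group-by-time interaction as its test, since the trial is sized on that. Moving to a single-visit endpoint would leave the sample size without a basis.
3. Code arm with two indicators, so that each programme arm has its own interaction with time against control. Test these two interactions with Holm at overall .05.
4. Choose one score for each other primary domain, including which self-efficacy questionnaire and which food measure. Test these in a fixed sequence within each contrast, at the alpha that contrast carries: for example, .025 per contrast once both SR interactions are rejected. The simpler alternative is Holm over all primary tests.
5. Label within-arm and per-visit comparisons as descriptive.
6. Restate the 80% as power per contrast.

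The cost is wording and some power. On the authors' formula, one contrast falls from 80% to about 71% at .025, or to about 76% under Holm if both effects are 0.25. Holm over all primary tests costs more: its first step with four outcomes and two contrasts is at .00625, where power for a given test is about 53%.
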